## Discussion

The introduction of minimal invasive endovenous ablation techniques has revolutionized the treatment of saphenous vein insufficiency. Different endothermal techniques have been introduced and tested in many prospective and randomized studies. Although most research is performed in GSVs, limited data on SSV is available. The results of endothermal techniques have proven to be excellent with a long-term anatomical success rate over 90%; therefore, the aim for future studies, especially in SSV, is diminishing heat-related complications, for example, pain and nerve injury, without compromising anatomical and clinical success. Until now the gold standard for the treatment of SSV insufficiency remains unclear.

This trial is designed to compare the anatomical success at 1 year after MOCA™ with RFA.

A secondary aim is to investigate whether MOCA™ is associated with a significant reduction in post-procedural pain. A major point of discussion is the choice for RFA above EVLA techniques. Although the meta-analysis of Van de Bos *et al*. showed the superiority of endothermal ablation (EVLA) in terms of anatomical success at 1 to 5 years follow-up [10], the more recent RCT of Rasmussen *et al*. has proven that the results of RFA using the ClosureFast device are at least similar to EVLT. In this randomized trial, RFA was associated with significantly less post-procedural pain compared to EVLA [24]. Furthermore, an important consideration in choosing ClosureFast is the uniformity of this technique, while in the case of ELVA, discussion about different tip designs and wavelengths might occur.

It has been proven that minimally invasive techniques will lead to a lower incidence of nerve injury in the SSV compared to conventional surgery (11% versus 28%). However, sural nerve injury is still considered a major and potentially underreported complication [25, 26]. Due to the fact that no heat and tumescent is used in MOCA™, nerve injury after SSV ablation might become a redundant complication.

In conclusion, the MESSI trial is a multicenter randomized controlled trial that aims to show a similar anatomical success of MOCA compared to RFA. Additionally, we hypothesize that this is accompanied by comparable clinical success and a reduction in post-procedural pain after MOCA™ compared with RFA.

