### Secondary endpoints

Post-procedural pain is evaluated using a 100-millimeter visual analog scale (VAS) during the first 2 weeks after treatment. The other secondary endpoints are initial technical success, clinical success, pain during treatment, complications and duration of the procedure. Initial technical success is defined as the ability to position the device adequately, treat the veins as planned and occlude the treated vein directly after the procedure proven by duplex ultrasonography. Clinical success is measured using the Venous Clinical Severity Score (VCSS). Complications related to the endovenous treatment, that occur within 30 days after treatment, are divided between major complications (deep venous thrombosis, pulmonary embolism, nerve injury, skin burn), minor complications (ecchymosis, superficial thrombophlebitis, hyperpigmentation, wound infection, prolonged pain >1 week) and sclerosans-related complications. Additionally, all endpoints will be evaluated at 2 and 5 years post-treatment.

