### Statistical analyses

The study results will be evaluated based on intention-to-treat analysis. Data concerning the 1, 2, and 5 years follow-up will be analyzed for both study groups on an intention-to-treat manner by student t-test (normal distribution) or Mann Whitney U-test (skewed distribution). To test for normality, the Kolmogorov-Smirnov test will be used. The Chi-square test will be used for binomial data. All probability values are two-tailed. *P* <0.05 will be considered significant. Obliteration rates will be presented as Kaplan Meier curves, including censoring in case of loss to follow-up.

An interim analysis will be performed after treatment and at 4 weeks follow-up for the first 80 patients to monitor the progression of the study. Final analysis will be performed after follow-up of the last patient included in this study is completed.

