### Definitions

Anatomical success is defined as occlusion of the treated SSV segment, measured with duplex ultrasonography.

Clinical success is defined as the objective improvement of clinical outcome after treatment, measured with the Venous Clinical Severity Score (VCSS).

Initial technical success is defined as the safe placement of the device at the predefined distance from the SPJ, treatment of the SSV without technical problems and occlusion of the treated SSV directly after treatment.

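### The hypothesis of comparable clinical success has no margin, and the only inference stated for it is a two-tailed difference test, which cannot show comparability

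*Protocol article*

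**What the plan says.** The Protocol article's Discussion ends by hypothesizing, beside similar anatomical success, that "Additionally, we hypothesize that this is accompanied by comparable clinical success and a reduction in post-procedural pain after MOCA™ compared with RFA".

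Under Definitions, "Clinical success is defined as the objective improvement of clinical outcome after treatment, measured with the Venous Clinical Severity Score (VCSS"). No cut-off for improvement and no expected rate is given, and the article does not say whether the endpoint is a yes/no outcome or a score. Under Secondary endpoints it is listed without special rank: "The other secondary endpoints are initial technical success, clinical success, pain during treatment, complications and duration of the procedure".

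Under Statistical analyses, proportions are handled thus: "The Chi-square test will be used for binomial data". Other data go to "student t-test (normal distribution) or Mann Whitney U-test (skewed distribution"). For all of these, "All probability values are two-tailed", and P "<0.05 will be considered significant".

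The Sample size calculation section has a non-inferiority range of 2%, but for occlusion only. Its two calculations concern occlusion and post-procedural pain. The abstract and Study objectives name two hypotheses, non-inferior anatomical success and less pain. Clinical success is in neither.

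**The concern.** A hypothesis of comparability says that one arm is not worse than the other by more than some tolerable amount. It is supported by excluding a larger deficit, not by failing to find a difference. The article applies this logic to occlusion, where it invokes non-inferiority and a range, but does not carry it over to the parallel clinical statement. There the stated tests can show that the arms differ. They cannot show that they are alike.

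The Discussion presents the aim for studies of this kind as less heat-related harm with no sacrifice of anatomical or clinical success, so the clinical half is part of the argument for MOCA. If a non-significant P-value were taken as support for it, the support would grow as the data became less informative: patients lost to follow-up and noisy VCSS scoring both make non-significance more likely. Repairing the test for the primary occlusion endpoint would not settle this, because the margin there does not apply to clinical success.

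**Working it through.** **Inputs from the article.** 74 evaluable patients per arm and 160 randomized 1:1 (Sample size calculation, Randomization); two-tailed P<0.05 with chi-square, t-test or Mann-Whitney (Statistical analyses).

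**The plan's own figure.** The 74 per arm was derived for occlusion: RFA 88%, MOCA 97%, margin 2%, one-sided 0.05, power 80%. The Farrington-Manning formula uses null rates restricted to differ by the margin, here 0.929 and 0.909.
- s0 = sqrt(0.929×0.071 + 0.909×0.091) = 0.386
- s1 = sqrt(0.88×0.12 + 0.97×0.03) = 0.367
- n = [(1.645×0.386 + 0.842×0.367) / (0.02 + 0.09)]² = 73.6, so 74 per arm
- 148 / (1 − 0.075) = 160

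The figure reproduces. It concerns occlusion and gives no assurance for clinical success.

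**Assumptions.** The article states no clinical success rate and no deficit that would matter. RFA rates from 80% to 97% and a 10-point deficit on MOCA are used below for illustration only.

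**If clinical success is a proportion.** The chance of a non-significant result under a true 10-point deficit was found by summing the exact binomial probabilities of all outcomes for which the uncorrected chi-square gives P>0.05.

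| RFA v MOCA | 74 per arm | 80 per arm (no losses) |
|---|---|---|
| 97% v 87% | 35% | 34% |
| 95% v 85% | 45% | 43% |
| 90% v 80% | 60% | 58% |
| 85% v 75% | 67% | 65% |
| 80% v 70% | 71% | 69% |

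Hand check at 90% v 80%, n = 74:
- pooled SE = sqrt(2×0.85×0.15/74) = 0.0587
- unpooled SE = sqrt((0.90×0.10 + 0.80×0.20)/74) = 0.0581
- power = Φ((0.10 − 1.96×0.0587)/0.0581) = Φ(−0.26) = 0.40, so 60% non-significant

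By the same approximation, the non-significance rate crosses 50% at an RFA rate of about 94% with 74 per arm and about 93% with 80. A Yates-corrected chi-square raises the 74-per-arm figures to 49% at 97%, 56% at 95% and 68% at 90%.

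**If VCSS is analysed as a score.** For a two-sample t-test with n = 74 per arm, the noncentrality is d×sqrt(74/2), with 146 degrees of freedom.

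| True deficit d | Noncentrality | Missed |
|---|---|---|
| 0.5 SD | 3.04 | 14% |
| 0.4 SD | 2.43 | 32% |
| 0.3 SD | 1.82 | 56% |

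**What an interval could exclude.** Approximate 95% half-widths at 74 per arm:
- score: 1.96×sqrt(2/74) = 0.32 SD
- proportion, both arms at 90%: 1.96×sqrt(2×0.9×0.1/74) = 9.7 points

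Suppose the rule is that the lower 95% Wald limit for MOCA minus RFA must lie above −10 points. With both true rates at 90% it is met about 54% of the time. With a true 10-point deficit (90% v 80%) it is met about 2.9% of the time.

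**The case against.** The strongest objection is about status. The article states its formal hypotheses in the abstract and in Study objectives, and clinical success is not among them. The quoted sentence is the last line of the Discussion, and an unpowered secondary endpoint without its own margin is ordinary. This stands and limits the weight. It does not remove the mismatch, because the sentence is worded as a hypothesis and the article commits to tests that cannot address it.

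Second, a reader might infer that the plan will treat P>0.05 as proof of comparability, or that the claim could be read only off a non-significant test. The article does not say so. It defines what counts as significant and is silent on how a non-significant result will be interpreted. It does not rule out an estimate with a confidence interval, and an unseen analysis plan may add one. The supportable statement is narrower: the one inference the article does state would not establish comparability.

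Third, a reader might infer that a 10-point loss would usually go undetected. The document gives no rate on which to base that. With the uncorrected chi-square it is true below an RFA rate of about 93–94% and false above it (45% at 95%, 35% at 97%). It also presumes a yes/no endpoint. The only VCSS results in the Background are scores (median 3 before treatment, 1 afterwards). On a score the trial detects a 0.5-SD deficit well, and nothing in the article shows that 0.3 SD would matter clinically.

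**Conclusion.** The point holds at modest weight. The article hypothesizes comparable clinical success, states only two-tailed difference tests at P<0.05 for it, and has no margin except the one for occlusion. A non-significant result would not support the hypothesis.

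The size depends on assumptions that the article does not supply. For a proportion, the chance that a 10-point deficit goes undetected runs from roughly a third at very high success rates to about 70% at 80%. For a score it is small at 0.5 SD and above half at 0.3 SD. Even the lower figures for the proportion are too high for non-significance to count as evidence of comparability. The primary sample size reproduces and is unaffected.

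**What to change.** In Statistical analyses, add that:

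- clinical success is reported as the between-arm difference in VCSS improvement at 1 year with a two-sided 95% confidence interval. Because a lower VCSS is better, the difference is signed so that positive values favour MOCA;
- the difference in the proportion with clinical success is reported in the same way, as supportive;
- P>0.05 is not evidence of comparability;
- clinical success is called comparable only if the interval excludes a deficit that the investigators fix before data are seen. Otherwise the result is reported as *no difference demonstrated*, with the interval.

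The score should lead because its interval of about ±0.32 SD can exclude a 0.5-SD deficit, whereas the proportion's interval at 90% success is almost as wide as 10 points. The 0.5-SD and 10-point values are illustrations; the steering committee must choose the deficit.

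The cost is a few sentences and an agreed margin. VCSS is already collected at screening and 1 year, so no patients or visits are added. The downside is that the secondary claim becomes harder to make: with a 10-point margin on the proportion, it would be met only about 54% of the time when both arms truly have 90% success.

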### Trial status

The MESSI trial began including participants in the second quarter of 2014. We expect that inclusion will be completed in the third quarter of 2015.

## Abbreviations

AE: adverse event
AVVQ: Aberdeen Varicose Vein Questionnaire
CEAP: clinical etiology anatomy pathophysiology
CRF: case report form
DSMB: Data Safety Monitoring Board
eGFR: estimated glomerular filtration rate
EVLA: endovenous laser ablation
GSV: great saphenous vein
IQR: interquartile range
MOCA™: mechanochemical endovenous ablation
RFA: radiofrequency ablation
SF-36: Short Form-36
SPJ: saphenopoplitial junction
SSV: small saphenous vein
VAS: visual analog scale
VCSS: Venous Clinical Severity Score.
